## Abstract

**Introduction:**

Psychosis spectrum disorders are characterized by both positive and negative symptoms, but whereas there is good effect of treatment on positive symptoms, there is still a scarcity of effective interventions aimed at reducing negative symptoms. Rumination has been proposed as an important and fundamental factor in the development and maintenance of symptoms across psychiatric diagnoses, and there is a need to develop effective interventions targeting rumination behaviors and negative symptoms in patients with psychotic disorders. The aim of the current study is to investigate the feasibility and acceptability of group rumination-focused cognitive behavioral therapy (RFCBT) in the treatment of young people with psychosis spectrum disorders as well as investigating potential indications of treatment efficacy.

**Methods and analysis:**

The study is a mixed-method clinical randomized controlled pilot trial with a target sample of 60 patients, who are randomized to either receive 13 weeks of group RFCBT or 13 weeks of treatment as usual (TAU). All patients are examined at the start of the project and at the 13-week follow-up. We will compare changes in outcomes from baseline to posttreatment between group RFCBT and TAU. In addition, qualitative analyzes are carried out to explore feasibility and acceptability and to uncover the patients’ experience of receiving the intervention.

## 1. Background

### 1.1 Introduction

Each year between 500 and 1000 people are diagnosed with schizophrenia or other psychotic disorders (collectively termed psychosis spectrum disorders) in Denmark. The disorder most often develops during the late teens and early adulthood [1] and typically debuts in the early 20s. Despite significant progress in treatment methods, including an increased focus on early intervention (counting e.g., the 2-year intensive outpatient treatment, OPUS, which is a permanent Danish psychiatric treatment service for young people with early-onset psychosis) and improved psychopharmacological treatment options, psychosis spectrum disorders are still considered among the most debilitating and expensive disorders in terms of lost workforce and costs of treatment [1–5].

Psychosis spectrum disorders are characterized by positive (delusions, thought disorders, hallucinations) and negative (blunted affect, alogia, anhedonia, asociality, and avolition) symptoms and cognitive disturbances (decreased attention, poor memory, and difficulty in planning). Whereas there is good effect of pharmacological treatment on positive symptoms, there is still a scarcity of effective interventions aimed at reducing negative symptoms and cognitive disturbances [6]. Although there is some evidence of an effect of cognitive remediation and social skills training, there is a need to develop effective interventions for negative symptoms are stressed by the fact that negative symptoms are strongly correlated with vocational and social outcomes, family burden, and quality of life along with being stable over the course of the illness and have a higher impact on later outcome than positive symptoms. Additionally, negative symptoms are strongly associated with depression and anxiety [7]. As much as 75% of patients with psychosis spectrum disorders experience depression and 65% experience anxiety symptoms [8–14]. Depression and anxiety are both strongly associated with relapse of psychosis and impaired social functioning, as well as negatively affected quality of life in people with psychosis spectrum disorders [8–15].

The co-occurrence of multiple psychological symptoms has motivated research aimed at identifying possible transdiagnostic phenomena, i.e., symptoms that are present across disorders and possibly fundamental to the experience of psychiatric symptoms. Rumination, which is characterized by persistent dwelling on negative emotions, problems, and unpleasant experiences, has been proposed as an important and fundamental factor in the development and maintenance of psychiatric symptoms across psychiatric diagnoses, such as depression [16, 17], anxiety disorders [16] and psychosis [18, 19] including both positive [16, 20–22] and negative symptoms [23]. For example, clinical case studies have shown that people with schizophrenia ruminate over the content of their delusions [24, 25], and negative symptoms, including social and emotional withdrawal, which can lead to isolation, and seem to both be worsened by, and increase the risk of, rumination in psychosis spectrum disorders [23].

Rumination can occur due to the individual’s attempt and desire to increase self-awareness and solve problems to prevent future mistakes [26]. However, it is suggested that rumination (as opposed to distraction) impairs problem-solving ability and reinforces/supports negative thinking [27] and access to negative memories [28]. The problem remains unsolved and can lead to frustration, stress, and intensify existing problems. Rumination is thus a behavior that induces avoidance behavior that consequently may contribute to increased passivity and worsened anxiety [29]. A self-blaming trait is often seen, which is why it is also a behavior that predicts depressive episodes and their length and severity [30].

Rumination-focused cognitive behavioral therapy (RFCBT) is a type of cognitive behavioral therapy (CBT) targeting rumination. The method differs from standard CBT by not directly challenging the patient’s thinking, and by focusing on a change in thinking style (from unconstructive ruminations to more constructive thinking and compassionate problem solving) rather than the actual content of the thinking. Randomized controlled trials (RCT) have shown that RFCBT reduces depressive symptoms and relapse rates in patients with depression [31] and in adolescents and young adults with elevated rumination behaviors. An RCT [32] has shown that a 6-session intervention targeting rumination in patients with psychosis significantly reduced paranoid delusions compared to standard treatment. Apart from this study RFCBT is, however, relatively unexplored in the treatment of psychosis spectrum disorders.

### 1.2 Aim and hypotheses

The aim of the current study is to investigate feasibility, acceptability and potential indications of treatment effect of group RFCBT in the treatment of young people with psychosis spectrum disorders that display symptoms of rumination.

We hypothesize that 1) group RFCBT will be feasible and acceptable for young people with a psychosis spectrum disorder undergoing OPUS treatment 2) RFCBT will decrease negative symptoms, depressive symptoms, rumination behaviour, and increase level of functioning.

We will use the knowledge generated by the present study in the design of a possible subsequent larger fully powered definitive randomized trial.

## 2. Methods and materials

### 2.1 Study design

The study is a mixed methods pilot RCT combining quantitative and qualitative methods. The study will enroll a total of 60 patients from Mental Health Center Glostrup, Mental Health Services in Capital Region of Denmark, which will be randomly assigned to one of the two arms: 1. Experimental group (13 weeks of standard (OPUS) treatment and group RFCBT) or 2. Control group (13 weeks of standard treatment (OPUS)). Patients are assessed at baseline (T1) and at treatment cessation (T2) (see Fig 1: SPIRIT schedule of enrollment). Following completion of post-treatment assessments, the patients in the control group will be offered RFCBT. The study is fulfilling the CONSORT criteria for non-pharmacological treatments and the extension to randomized pilot and feasibility trials.

**Fig 1 pone.0297118.g001:**
[figure not shown]
SPIRIT schedule of enrollment.

To best explore the aim and provide the most well-informed basis for possible subsequent protocol for a larger RCT, the current trial combines quantitative and qualitative methods. The value of qualitative research in the development and evaluation of complex interventions is widely recognized in psychiatry research [33, 34], and the combination with quantitative methods will enable not only an indication of the potential clinical relevance of the intervention, but also the organizational and individual prerequisites needed for successful implementation and optimal benefit of the intervention.

The planned study period is from August 1^st^, 2023—December 31^st^, 2024.

### 2.2 Participants

The trial is aimed at young people between the ages of 18–35 allocated to OPUS treatment based on a diagnosis of first episode psychotic disorder or schizotypal personality disorder. The following eligibility criteria apply:

**Table pone.0297118.t001:** 

*Inclusion criteria*
Age 18–35 Diagnosed with a psychosis spectrum disorder (ICD-10 F2x) At least 8 months left of their OPUS treatment The presence of rumination behavior as assessed by a score of minimum 30 on the Perseverative Thinking Questionnaire (PTQ) [35] Danish-speaking
*Exclusion criteria*
Substance abuse or positive symptoms that make participation in therapy difficult Severe suicidal thoughts/behavior Not capable of providing informed consent Mild, moderate, or severe intellectual disability (IQ ˂ 70) Planned adjustment of antidepressant and/or antipsychotic treatment (noted in the patient’s medical record)

### 2.3 Sample size

As the overall purpose of the study is to uncover acceptability, feasibility and provide indications of a possible treatment effect. the number of subjects is not based on a calculation of statistical power, but rather on an expectation of how many will be able to include over a project period of 18 months A total of 30 patients receiving the intervention will be compared to 30 receiving standard treatment. A sample size of 30 participants is considered adequate for a pilot-study assessing feasibility, acceptability, and providing indications of efficacy of an intervention [36].

The study is situated at Mental Health Center Glostrup, which has approximately 300 active OPUS patients. In previous trials with group-based CBT in OPUS, it has been possible to recruit a minimum of 10% of the total OPUS sample, thus it is realistic to include the 60 patients in a project period of 18-months.

### 2.4 Randomization

The randomization is done via the computerized randomization function in Research Electronic Data Capture (REDCap) [37] tool in ratio 1:1 on the basis of an uploaded block randomization list (block size 4–6) generated by an external party. In addition, stratification is used to ensure equal distribution of gender between the groups.

### 2.5 Procedure

The study is carried out within the framework of OPUS. OPUS is a 2-year intensive outpatient treatment service for patients aged 18–35 with a psychosis spectrum disorder. Patients meeting the listed eligibility criteria will routinely be approached about participating in this clinical trial. Following inclusion, the participants will have a baseline assessment and be randomized to one of the two treatment arms. Posttreatment assessments will be conducted at treatment cessation (see Fig 2 consort diagram). Among the patients who are allocated to the intervention group, some will also be invited to take part in a qualitative interview. This recruitment strategy presents the risk of healthy volunteer bias. However, our experience from previous similar studies is that this is a minimal limitation in the current setting.

**Fig 2 pone.0297118.g002:**
[figure not shown]
Consort diagram. N = number of participants, RFCBT = Rumination-focused cognitive behavioral therapy TAU = Treatment As Usual.

### 2.6 Qualitative sub-study

Individual semi-structured interviews with purposefully sampled participants allocated to the experimental group will be carried out at baseline (focusing on motivation for participation) and repeated posttreatment after approximately three months (focusing on experience of participation). To ensure maximum variation, participants will be sampled according to age, gender and rumination severity, and an interview schedule including open-ended questions and probing is used to support information richness. The information power (i.e., data saturation) is assessed after interviews with 10–12 patients and additional 3–5 interviews will be conducted if needed. For patients who drop out of the intervention before the end of the intervention, the reasons for this are carefully requested. Furthermore, all participants in the intervention group are invited to a concluding group interview. Consequently, a total of three group interviews will be conducted, with a maximum of ten participants per group.”

The purpose of the group interviews is to facilitate discussion and collective evaluation among the participants Finally, interviews with the two therapists responsible for the interventions will be carried out.

## 3. Intervention

### 3.1 Experimental group

The experimental intervention consists of group-based, manualized RFCBT that follows the principal treatment components outlined in the treatment manual developed and published by Watkins [26]. The manual has been translated for use in a Danish context [38]. The treatment comprises 11 groups-session and two individual sessions and is expected to last approximately three months. The treatment is offered as an add on to standard OPUS treatment (2-year intensive outpatient treatment). Before initiating the group sessions, an individual preparatory session (one hour) will take place. This is followed by 11 group sessions of (2 hours/once a week). The intervention ends with an individual session (one hour duration).The therapy includes review and completion of hand-outs, psychoeducation, or dissemination of important messages from the manual, practical exercises, and behavioral experiments (patients cooperate in pairs), guided visualization exercises as well as dialogue and exchange of experiences. RFCBT is based on the theoretical conception, that rumination can be seen as a mental-habit. It uses functional analysis to help people change the habits of rumination and avoidance behavior by identifying triggers and practice alternative behaviors to these cues. Guided visualization is used in the group therapy sessions to motivate and engage the participants in behavior change. The participants conduct small behavioral experiments between the sessions to test the applicability of the alternative behavior in their everyday life. A primary goal is to acquire skills so that one does not automatically fall into the habit of ruminating or avoiding. The intervention takes place in OPUS and is overseen by an experienced psychologist (experiment leader) and a co-therapist.

### 3.2 Control group

Patients in the control group receive standard OPUS treatment and are offered the experimental intervention on completion of follow-up assessment (expected at 3 months). OPUS treatment is handled by an interdisciplinary OPUS team and consists primarily of medical treatment, psychoeducation, training in symptom management and social skills as well as family involvement/ treatment. All patients in OPUS have a contact doctor and a contact person who is responsible for coordinating the treatment and collaborating with municipal bodies.

## 4. Assessments procedures

Questionnaires and measurements are completed at baseline and repeated at treatment cessation after approximately three months. Follow-up clinician-administered measurements are conducted by investigators blind to group allocation. Patients will be instructed not to disclose their allocation prior to post-treatment assessments. In case an assessor is unblinded, the assessment will be conducted by another assessor. The assessors will be psychology master students. All assessors will receiving adequate training prior to conducting the assessments. The assessors will attend regular inter-rater reliability training on key measures in the battery. Quantitative data are collected in REDCap [37] and qualitative data are audiorecorded on a dictaphone and subsequently transcribed ad verbatim and anonymized.

## 5. Outcomes

### 5.1. Feasibility and acceptability

Feasibility and acceptability will be defined as:
A recruitment rate of 20% of the eligible OPUS patients.A therapy completion rate of ≥80% of the recruited participants in the RFCBT group.80% of the patients in the RFCBT group reporting a satisfaction rating of ≥20 on the eight item Client Satisfaction Questionnaire [39].Feasibility and acceptability will be further assessed by qualitative interviews with patients in the RFCBT groups, as well as key informants from the staff, including questions on:
Reasons for non-participation and any dropouts during the interventionThe organizational and individual prerequisites needed for successful implementation and optimal benefit of the intervention.Expenses (hourly consumption, transport, etc.) associated with carrying out the intervention.

### 5.2 Treatment effect

#### Primary outcome

Negative symptoms:

Negative symptoms will be assessed using the Brief Negative Symptoms Scale (BNSS) [40]. The BNSS covers six domains of negative symptoms including anhedonia, lack of normal emotional discomfort, asociality, avolition, dampened affect, and alogia. The score is based on 13 questions scored on a 0 (the symptom is absent) to 6 (the symptom is severe) scale. Thus, the total score ranges from 0–78 with higher scores indicating greater impairment/presence of negative symptoms.

#### Secondary outcomes

Worry/rumination behavior:

The frequency of rumination is measured using the Perseverative Thinking Questionnaire (PTQ). The PTQ is a self-reported questionnaire and includes 15 questions; each question is scored from 0 (never) to 4 (always) [35], resulting in a total score of 0–60.Frequency of rumination in relation to depressive symptoms is measured using the Ruminative Response Scale (RRS). The RRS is a self-reported questionnaire and includes 22 questions that are rated on a 4-point Likert scale ranging from 1 (never) to 4 (always) giving a total score of 22–88 with higher score indicating more severe rumination [41].

Positive symptoms:

The presence of positive symptoms is assessed using the Scale for the assessment of positive symptoms (SAPS) [42], that covers the four subdomains hallucinations, delusions, bizarre behavior and linguistic (formal) thought disorder. The scale includes 34 items rated from 0–5, giving a total score of 0–170.

Function level:

Level of functioning is measured using the Social Functioning Scale (SFS) questionnaire [43], that contains seven subscales: withdrawal/social engagement, interpersonal communication, independent-achievement, independent-competence, recreational, prosocial, and job/employment. The questionnaire has 76 items which are scored from 0 (never) to 3 (often), giving a total score of 0–228, with higher scores indicating better functioning.

Depression:

Depressive symptoms are assessed using the Calgary depression scale (CDS) [44] in the form of a structured interview. Items are scored 0–3 on a total of nine questions related to moodiness, hopelessness, self-deprecation, self-attributing notions of guilt, pathological guilt, morning depression, early morning awakening, suicide and observed depression. The total score ranges from 0–27 with higher scores indicating higher severity of depressive symptoms. The scale has been validated for measuring depression in patients with schizophrenia.

Executive function

Executive function is measured using the Behavior Rating Inventory of Executive Function (BRIEF) questionnaire [45] consisting of 75 statements that express function in the areas of impulse inhibition, flexibility, emotional control, self-monitoring, initiation, working memory, planning/organization and organization of Materials. Each statement is scored from 1–3, giving a total score of 75–225, with higher scores indicating poorer functioning.

To encourage participants to provide honest and accurate answers and thereby minimize reporting bias, it will be emphasized that their responses will be kept confidential and anonymous. Self-report questionnaires include a risk of reporting bias. However, we attempt to minimize this by including indirect questioning and questions about their behavior rather than their beliefs. Indirect questioning refers to a method of asking questions that does not directly inquire about a specific piece of information but rather seeks to obtain that information indirectly. That is, instead of asking a straightforward or direct question, individuals use a more subtle or circuitous approach to gather the desired information. This approach is used to create a more comfortable atmosphere, minimizing the chances of biased or inaccurate responses due to the pressure of direct questions. By sidestepping direct queries, it helps foster honesty and reduces reporting bias, where the way questions are framed impacts the truthfulness of answers.

## 6. Analyses

### 6.1 Quantitative analysis

Treatment effect will be analyzed as changes in outcome measures from baseline to post-treatment in the RFCBT group using paired samples t-tests or a corresponding non-parametric test such as Pearson’s chi-square test. Continuous data are presented as mean ± standard deviation (SD). A two-sided significance level of p <0.05 is used.

The estimated pooled standard deviation from both groups in this pilot study will be used to inform the sample size calculation for a fully powered RCT.

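### Section 6.1 tests the treatment effect within the RFCBT arm only, which contradicts the promised RFCBT versus TAU comparison and would credit shared change to RFCBT

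*Protocol article*

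**What the plan says.** Three places in the protocol article describe how efficacy will be judged, and they do not agree.

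- Section 6.1, the only quantitative analysis section: "Treatment effect will be analyzed as changes in outcome measures from baseline to post-treatment in the RFCBT group using paired samples t-tests". It adds "A two-sided significance level of p <0.05 is used" and names no between-arm test. It uses both groups only for the pooled standard deviation meant for planning a later trial.
- Abstract, Methods and analysis: "We will compare changes in outcomes from baseline to posttreatment between group RFCBT and TAU".
- Section 2.3: "A total of 30 patients receiving the intervention will be compared to 30 receiving standard treatment".

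The design serves a between-arm contrast. Patients are allocated "in ratio 1:1 on the basis of an uploaded block randomization list" and "stratification is used to ensure equal distribution of gender between the groups" (section 2.4), and follow-up clinician ratings are blinded (section 4). Both arms receive OPUS (sections 2.1 and 3.2). BNSS is the primary outcome for treatment effect and PTQ a secondary one (section 5.2). A PTQ score of at least 30 is an inclusion criterion (section 2.2), while BNSS has no entry threshold.

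**The concern.** A paired test in one arm asks whether RFCBT patients changed. It does not ask whether they changed more than they would have under OPUS alone. OPUS is itself an intensive treatment with medication, psychoeducation and skills training, so some change over 13 weeks without RFCBT is plausible, and the one-arm test attributes all of it to RFCBT. Randomisation, stratification and blinded rating then add nothing to the efficacy result.

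Two analysts could also follow the same article to different analyses, one from section 6.1 and one from the abstract. The result matters even in a pilot: section 1.2 hypothesises that RFCBT will reduce negative symptoms, and a p-value criterion is attached to the test.

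**Working it through.** There is no planned power figure to reproduce: section 2.3 says that "the number of subjects is not based on a calculation of statistical power". From the documents come 30 patients per arm and a two-sided level of 0.05. Every other input below is an assumption, because the article gives no means, SDs or correlations. All figures take 30 complete pairs per arm.

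**1. False-positive rate of the section 6.1 test under shared change.** Let the true RFCBT minus TAU effect be zero and let both arms change by dz = mean change / SD of change. The paired t statistic then follows a noncentral t distribution with 29 degrees of freedom and noncentrality dz × √30. The critical value is 2.045.

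| Assumed shared dz | Noncentrality | Rejection rate |
|---|---|---|
| 0 | 0 | 5% |
| 0.1 | 0.55 | 8.3% |
| 0.2 | 1.10 | 18.5% |
| 0.3 | 1.64 | 35.5% |
| 0.5 | 2.74 | 75.4% |

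A between-arm comparison of change cancels any shift common to both arms, so its rate stays at the nominal 5% in every row.

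**2. Regression to the mean on PTQ.** Suppose the qualifying score is also the T1 score. Take an unselected clinic mean μ of 28 to 32, SD of 10 to 12 and retest correlation r of 0.6 to 0.8. For a normal score truncated at 30, the expected fall without any treatment effect is (1 − r) × (E[X | X ≥ 30] − μ). Dividing by the SD of change gives dz, and the rejection rate follows as in step 1.

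- Lowest rate: μ = 32, SD 10, r = 0.8. Selected mean 38.75; fall 0.2 × 6.75 = 1.35 points; SD of change 6.13; dz 0.22; rejection 21%.
- Largest fall: μ = 28, SD 12, r = 0.6. Selected mean 38.88; fall 0.4 × 10.88 = 4.35 points; SD of change 9.99; dz 0.44; rejection 64%.
- Highest rate: μ = 28, SD 10, r = 0.6. Selected mean 37.29; fall 0.4 × 9.29 = 3.72 points; SD of change 8.32; dz 0.45; rejection 66%.

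In 4,000 simulated trials per setting at SD 12, the between-arm test of change rejected in 4.3% to 5.8%.

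If PTQ is instead measured afresh at T1, the regression falls wholly or partly between screening and T1. With a stable true score and independent errors, the expected T1 to T2 fall is zero and the rate returns to about 5%. The range for PTQ is therefore about 5% to 66%.

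**3. Precision of a between-arm analysis.** With 30 per arm, the 95% CI half-width in SD units, assuming equal SDs at T1 and T2 and a pre-post correlation of 0.6, is:

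- T2 scores alone: 2.002 × √(2/30) = 0.52
- Change scores: 0.517 × √(2 × (1 − 0.6)) = 0.517 × 0.894 = 0.46
- ANCOVA: 0.517 × √(1 − 0.6²) = 0.517 × 0.8 = 0.41

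**The case against.** The strongest reply is that the article does commit to a between-arm comparison, in the abstract and in section 2.3, and that section 6.1 itself draws on both groups for the pooled SD. A reader might infer that the control arm is never used, or that a biased result is certain to be reported. The documents support neither. They support a contradiction, with harm if section 6.1 prevails.

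A reader might also infer that regression to the mean is built into the results generally. It is not. BNSS has no entry threshold, so the direct argument concerns PTQ and, to a lesser degree, measures correlated with it. Section 2.5 places the baseline assessment after inclusion, and the article does not say whether the screening PTQ is reused.

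The size of shared change in BNSS is unknown. Section 1.1 describes negative symptoms as stable, which favours the lower rows of the first table. The only quantity that section 6.1 carries into the next trial's sample size is the pooled SD, not the within-arm effect. Handling of missing T2 data belongs in an analysis plan and is no part of this point. A change-score comparison, as the abstract promises, would already remove shared drift, so ANCOVA is a preference and not a necessity.

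All of this limits the claim but leaves its core. The one section that specifies a test specifies one that omits the comparator. That is an analysis stated wrongly, not a detail left for later.

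**Conclusion.** The point holds, and section 6.1 must be corrected. As written, its treatment-effect test excludes TAU and conflicts with the abstract and section 2.3. If it is followed, even a small shared change of 0.1 to 0.2 SD of change raises the false-positive rate to 8% to 18.5%, and a moderate one of 0.3 to 0.5 raises it to 36% to 75%. These rates are conditional on the assumed shared change; the article gives no basis for choosing a value, least of all for BNSS. If the shared change is an improvement, the error favours RFCBT. The extra inflation for PTQ lies between none and a rate of 66%, depending on how T1 is obtained and on the assumed mean, SD and retest correlation.

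**What to change.** Replace the sentence in section 6.1 with wording such as: *The treatment effect is the RFCBT minus TAU difference at T2, with a 95% CI, estimated by ANCOVA of the T2 score adjusted for its baseline value and for gender, the stratification factor. All randomised patients are analysed in their allocated arm. Within-arm changes are reported descriptively, without p-values.* A between-arm comparison of change scores would also be valid, but less precise.

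Align the abstract and section 2.3 with this text, and state whether the screening PTQ score serves as T1.

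The cost is wording only, since both arms are already assessed at T1 and T2. The reported effect may look smaller than an uncontrolled change, and at this sample size its interval will be wide.

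### Section 6.1 names Pearson's chi-square as the non-parametric counterpart of the paired t-test, but it is not a test of change in paired scores

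*Protocol article*

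**What the plan says.** Section 6.1 of the protocol article defines the treatment-effect analysis as "changes in outcome measures from baseline to post-treatment in the RFCBT group using paired samples t-tests", and then allows an alternative: "or a corresponding non-parametric test such as Pearson’s chi-square test". The threshold is stated as "A two-sided significance level of p <0.05 is used".

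The outcomes are set out in section 5.2. For the primary outcome, the BNSS, the article states: "Thus, the total score ranges from 0–78 with higher scores indicating greater impairment/presence of negative symptoms". The six secondary measures are also total scores: PTQ 0–60, RRS 22–88, SAPS 0–170, SFS 0–228, CDS 0–27 and BRIEF 75–225. Section 4 has each measure taken at baseline and again about three months later in the same patients.

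Section 5.2 defines no categorical effect outcome, cut-point or responder rule. No paired non-parametric test, such as the signed-rank, sign or McNemar test, is named anywhere.

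**The concern.** A paired t-test asks whether the mean within-patient difference is zero. Its usual rank-based counterpart is the Wilcoxon signed-rank test. Pearson's chi-square asks whether two categorical variables are associated, using counts from independent observations. It cannot be applied to these scores until someone cuts them into categories, and the article gives no rule for that.

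Once cut, the scores can be tabulated in two ways, and both fail:

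- **Visit by category.** Baseline and post-treatment values are treated as if they came from different patients. The pairing is ignored.
- **Baseline category by post-treatment category, same patients.** The test then asks whether a patient's score at one visit predicts the score at the other. A stable scale would give a significant result with no change at all.

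At stake is the reading of the effect results if the fallback is used. The first table tends to hide real change. The second can be mistaken for evidence of change where there is none. The article also leaves the choice of cut-point and table open until after the data are seen.

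**Working it through.** The article states no power, effect size or correlation, so there is no figure of its own to reproduce.

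**Inputs from the article**
- Pairs in the RFCBT arm: 30 (section 2.3, "A total of 30 patients receiving the intervention will be compared to 30 receiving standard treatment"; section 2.4, "in ratio 1:1 on the basis of an uploaded block randomization list").
- Alpha: 0.05, two-sided (section 6.1).
- Reduced number of pairs for a sensitivity run: 0.80 × 30 = 24, from the target in section 5.1, "A therapy completion rate of ≥80% of the recruited participants in the RFCBT group". Using the therapy-completion target as a stand-in for available pairs is an assumption.

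**Assumptions not in the article**
- Bivariate normal baseline and post scores, correlation rho from 0 to 0.8.
- True mean change of 0, 0.3 or 0.5 SD.
- Scores split at the baseline population median; chi-square on 1 degree of freedom without continuity correction.
- 20,000 simulated trials per setting.

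**Use (a): the two visits treated as independent samples, n = 30**

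| rho | Type I error, chi-square | Power at 0.5 SD, chi-square | Power at 0.5 SD, Wilcoxon | Relative loss |
|---|---|---|---|---|
| 0 | 0.053 | 0.330 | 0.454 | 1 − 0.330/0.454 = 27% |
| 0.3 | 0.030 | 0.311 | 0.593 | 1 − 0.311/0.593 = 48% |
| 0.5 | 0.015 | 0.294 | 0.735 | 1 − 0.294/0.735 = 60% |
| 0.7 | 0.006 | 0.268 | 0.916 | 1 − 0.268/0.916 = 71% |
| 0.8 | 0.003 | 0.248 | 0.985 | 1 − 0.248/0.985 = 75% |

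For a 0.3 SD change the relative losses are 20%, 52%, 69%, 85% and 91% in the same order. Wilcoxon keeps its type I error at 0.045 to 0.050 throughout. Its power at 0.5 SD is within about 2 points of the paired t-test (0.466, 0.613, 0.754, 0.929, 0.988).

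The type I column can be checked by formula. For a median split of normal scores, the correlation of the two binary indicators is phi = (2/π) × arcsin(rho). The true variance of the difference in proportions is (1 − phi) times what chi-square assumes, so type I error ≈ P(χ²₁ > 3.84/(1 − phi)). At rho 0.5, phi = 0.333, 3.84/0.667 = 5.76, and the tail probability is 0.016. At rho 0.8, phi = 0.590, 3.84/0.410 ≈ 9.4, and it is 0.002. Both agree with the simulation.

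**Use (b): same-patient baseline-by-post cross-table, n = 30, no true change**

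| rho | 0 | 0.3 | 0.5 | 0.7 | 0.8 |
|---|---|---|---|---|---|
| Rejection rate | 0.048 | 0.175 | 0.434 | 0.792 | 0.929 |

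The reason is visible in the formula: the statistic is driven by √30 × phi, which contains no change term. At rho 0.5 this is 5.477 × 0.333 = 1.83, giving a rejection probability of about 0.45, close to the simulated 0.434.

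**With 24 pairs** the pattern is the same. At rho 0.5, use (a) has type I error 0.021 and power 0.250, against 0.624 for Wilcoxon at 0.5 SD. Use (b) rejects 40% of the time under no change.

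**The case against.** The strongest reply concerns weight, not correctness. The main test is the paired t-test. Chi-square is one example of a fallback, introduced by 'such as', so nothing goes wrong unless the t-test is set aside and the example is followed literally. Section 1.2 makes this a study of feasibility, acceptability and possible signs of effect, and section 2.3 says that "the number of subjects is not based on a calculation of statistical power". The quantity carried into the next trial is the pooled SD, which this test does not touch. All of this stands, and it limits severity.

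It is also fair that the fallback may seldom be needed. The paired t-test depends on the differences, not on the shape of the raw scores. In a check with skewed scores bounded at 0–78 (assumed beta(1.2, 4) shape, 30 pairs, rho 0 to 0.7), its type I error stayed at about 0.05 and its power was within about 3 points of Wilcoxon. The simulations in the working use normal scores, where the t-test would be kept, so they illustrate the test's behaviour and do not forecast the trial's results.

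Two replies do not stand. One is that the detail belongs in an analysis plan that is not shown: the article names a test, and the test is the wrong one. The other is that chi-square was meant for categorical variables: the sentence is about change in the outcome measures, calls the test a counterpart of the paired t-test, and no effect outcome is categorical.

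A reader might infer that the fallback always loses most of the power, or always errs towards hiding change. The article supports neither. The loss depends on a correlation that it does not give, and the direction of the error depends on a table that it does not specify.

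**Conclusion.** The point holds: the named fallback is not a valid test of paired change in any of the seven effect outcomes, and nothing elsewhere in the article corrects it. That conclusion follows from the text and needs no simulation.

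The numerical size is conditional on the assumed normal scores, median split and correlation. Treated as independent samples, the test is close to nominal at rho 0 and increasingly conservative as rho rises. Its power loss at 0.5 SD is about a quarter at rho 0, about half at rho 0.3 and 60–75% at rho 0.5–0.8. As a same-patient cross-table it over-rejects heavily for any appreciable correlation.

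Severity is moderate, since the harm arises only if the fallback is used and the trial is a pilot without a power calculation. The same sentence in section 6.1 tests change within the RFCBT arm only, although the abstract promises a comparison with TAU. That is a separate issue, and correcting the fallback does not resolve it.

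**What to change.** In section 6.1, replace Pearson's chi-square with the Wilcoxon signed-rank test as the non-parametric alternative for paired scores. State that chi-square or Fisher's exact test is kept for independent categorical comparisons only. If a paired binary outcome is ever defined, McNemar's test would be its counterpart.

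The cost is one phrase in one sentence. No change to design, sample size or data collection follows.
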